### Interventions

2.9

Patients in the experimental group use *Baidu Jieduan Granule* together with conventional Western medicine, while the control group accept standard Western medicine only. The *Baidu Jieduan Granule* comprises *Scutellariae Radix* (30 g), *Radix Rhei Et Rhizome* (15 g), *Gypsum Fibrosum* (45 g), *Cmnamomi Mmulus* (9 g), *Polygoni Cuspidati Rhizoma Et Radix* (30 g), *Verbenae Herb* (3 g), The *Baidu Jieduan Granule is* brownish yellow particles and provided by Beijing Kangrentang Pharmaceutical Co. LTD (Number: Jing 201800603), which is one of the biggest companies specializing in the production of Chinese medicine Granules.

### Outcomes and measurements

2.10

#### Primary outcomes

2.10.1

The primary outcomes of our study are clinical outcomes. In our study, there are 4 kinds of clinical outcomes:

1.recovery, the following conditions shall be met:1.the body temperature is normal for 3 consecutive days2.respiratory symptoms disappeared completely,3.the nucleic acid test of respiratory tract samples is negative for 2 consecutive times (the sampling interval is at least 1 day);2.condition improved, meet any of the following 2 items:1.the clinical symptoms are significantly relieved,2.the nucleic acid of sputum, nasopharynx test paper and other respiratory tract samples are negative for 2 consecutive times (the sampling interval should be at least 24 hours);3.condition worsen, one of the following situations occurs:1.shortness of breath, respiratory rate (RR) ≥30 times/minutes,2.oxygen saturation ≤93% in resting state,3.arterial oxygen partial pressure (PaO2) / fraction of inspired oxygen (FiO2) ≤300 mm Hg,4.shock,5.respiratory failure, requiring ventilator support,6.organ failure needing intensive care, and7.death.

We count the number of patients of each kind of clinical outcomes then calculate the ratio.

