### Study design and settings

2.1

This research is designed as a multicenter prospective cohort study conducted at 4 medical centers, including Huangshi Hospital of TCM (Huangshi City, Hubei Province), LaoHeKou Hospital of TCM (LaoHekou City, Hubei Province), Hubei Provincial Hospital of TCM (Wuhan City, Hubei Province) and LongHua Hospital Shanghai University of TCM (Shanghai City, Shanghai). LongHua Hospital Shanghai University of TCM is the leading medical center. These 4 TCM hospitals are the main medical institutions responsible for the treatment of COVID-19 patients. In order to strengthen the cooperation, we will establish a coordination center. This center contains medical experts, statisticians and quality control experts from other hospitals and universities. The primary function of this center is to provide vital clinical decisions or recommendations, conduct data statistic, monitor the research process.

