#### Second outcomes

2.10.2

1.Vital signs (d1-14), temperature, heart rate, blood pressure, respiratory rate (RR), oxygen saturation.2.Chest computed tomography (CT) score (d1, d7, d14), in our study we use high resolution computed tomography (HRCT). According to the existing scoring standards,^[22,23]^ each lobe will be graded. 0 points = no pathological changes of lung lobe, 1 point = pathological changes in 0% to 25% of lung lobes, 2 points = pathological changes in 25% to 50% of lung lobes, 3 points = pathological changes in 50% to 75% of lung lobes, 4 points = pathological changes in 75% to 100% of lung lobes, the total score of 5 lobes is used as the chest CT lesion score of each patient. We compare the mean value of lung CT scores.3.Inflammatory index (d1, d3, d5, d7, d14): peripheral hemogram (the count of peripheral blood leukocyte and lymphocyte), C-reactive protein (CRP), procalcitonin (PCT), tumor necrosis factor (TNF-a), interleukin-6 (IL-6), interleukin-10 (IL-10).4.Main organ function (d1, d3, d5, d7, d14): alanine aminotransferase (ALT), aspartate aminotransferase (AST), total serum bilirubin (STB), blood urea nitrogen (BUN), serum creatinine (Cr).5.Coagulation index (d0, d7, d14): blood platelet count (PLT), D-dimer, activated partial thromboplastin time (APTT), prothrombin time (PT), fibrinogen (Fg).6.Acute Physiology and Chronic Health Evaluation (d1, d3, d5, d7, d14, APACHE-II, Additional file 2) score: we compare the mean value of APECHA II the scores between 2 groups, and calculate improvement rate in APECHA II score = (d14 scored-0 score)/d0 score.

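### Symptom relief, with no threshold stated, is enough by itself for the primary category 'condition improved', in an add-on comparison with no placebo or masking described

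*Protocol article*

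**What the plan says.** Section 2.10.1 (Primary outcomes) sorts patients into outcome categories. The middle category, improved, is met by either of two items. The first is "the clinical symptoms are significantly relieved"; the second item is two consecutive negative respiratory nucleic acid tests. The top category is stricter: "recovery, the following conditions shall be met", and its list joins normal temperature, complete disappearance of respiratory symptoms and two negative tests. The summary is by category: "We count the number of patients of each kind of clinical outcomes then calculate the ratio".

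Section 2.8 (Grouping) forms the groups by whether patients use the granule, matched on gender, age and basic diseases. Under section 2.9 (Interventions) the experimental group receives the granule together with conventional Western medicine, "while the control group accept standard Western medicine only". No placebo is described.

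Section 2.10.2 (Second outcomes) grades the share of each of five lobes that is affected, on a scale of 0 to 4, and adds the grades: "We compare the mean value of lung CT scores". The article does not say who grades the scans or classifies the outcomes, or whether those people know the group.

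**The concern.** The two items are alternatives, so an impression of marked relief decides the category even when nucleic acid tests are still positive or have not been done. Nothing in the article fixes how much relief is enough, which symptoms count or who judges. Patients and treating clinicians can be expected to know who takes the granule. The Introduction already describes the product as effective and safe and gives proof of its efficacy as an aim. If expectation has any effect on the judgement, the plausible direction is towards more improved patients in the granule group.

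Such an error arises when the outcome is measured. Matching on baseline characteristics leaves it in place, and so would any adjustment for confounders. A difference in the primary outcome could then appear without any drug effect. CT grading, as a visual estimate, is open to the same influence if readers know the group or the visit day.

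**Working it through.** The plan gives no figure to reproduce: section 2.7 states that the sample size could not be calculated and gives no event rates. The check is a reading of the rule, followed by an illustration of how sensitive the comparison is.

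**Reading the rule**

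| Route | Negative nucleic acid tests needed? | Symptom judgement |
|---|---|---|
| Recovery | Yes, two | Needed, not sufficient |
| Improved, symptom item | No | Sufficient alone |
| Improved, test item | Yes, two | Not needed |

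The symptom item of *improved* is the one route to a better category that requires no laboratory result.

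**Illustration**

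Inputs from the article:
- 300 patients at 1:1 (sections 2.3 and 2.8) and about 10% withdrawal (section 2.7): 300 × 0.9 / 2 = 135 per group.
- Chi-squared test for rates and P < .05 (section 2.12).

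Assumptions, not in the article:
- The test is two-sided and uncorrected.
- Recovery and improved are pooled as one good outcome.
- The true pooled rate p is the same in both groups.
- A fraction m of all other granule patients is called relieved.

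The observed granule rate is q = p + m(1 − p). With p = 0.70:
- m = 10%: q = 0.70 + 0.10 × 0.30 = 0.73
- m = 20%: q = 0.70 + 0.20 × 0.30 = 0.76
- m = 30%: q = 0.70 + 0.30 × 0.30 = 0.79

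The false-positive rate is the sum, over all pairs of counts, of Bin(x₁; 135, q) × Bin(x₂; 135, p) where the chi-squared test rejects. With m = 0 it is about 5%.

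| True rate p | m = 10% | m = 20% | m = 30% |
|---|---|---|---|
| 60% | 0.107 | 0.279 | 0.549 |
| 70% | 0.086 | 0.201 | 0.400 |
| 80% | 0.071 | 0.138 | 0.260 |

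Normal approximation as a check for p = 0.70, q = 0.76:
- pooled rate = 0.73
- critical difference = 1.96 × √(2 × 0.73 × 0.27 / 135) = 0.106
- standard error = √((0.76 × 0.24 + 0.70 × 0.30) / 135) = 0.0539
- rejection probability = Φ((0.06 − 0.106) / 0.0539) + Φ((−0.06 − 0.106) / 0.0539) ≈ 0.198, against 0.201 exact.

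**Patients who cannot be upgraded**

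If a share w of the other patients meets the worsening criteria and cannot be moved, the rise becomes m(1 − w)(1 − p). With w = 50% (assumption), m = 20% and p = 0.70 it is 0.20 × 0.50 × 0.30 = 0.03. The observed rate is then 73% and the false-positive rate about 9% rather than 20%.

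**The case against.** The strongest reply has four parts.

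- **Silence is not absence.** A reader might infer that outcome assessment is stated to be unmasked. It is not: the article is silent, and the full protocol and the case report form (CRF, Additional file 5) are not shown. This stands, so the exact wording is that no masking is described. The sufficiency of the symptom item does not rest on that silence, because section 2.10.1 states it.
- **The pooled outcome is not the plan's.** The article counts each category and never combines recovery with improved. This stands, and the figures above are therefore illustrative. The improved count is exposed with or without pooling.
- **The illustration is generous.** Worsening is mostly defined by objective criteria such as respiratory rate, oxygen saturation, PaO2/FiO2, ventilator support and death. An impression of relief is unlikely to move those patients. This stands, and it lowers the figures as shown.
- **Masked review afterwards would not cure it.** A reader might infer that the coordination center could settle the matter by reclassifying CRF extracts with the group removed, since section 2.1 says "This center contains medical experts, statisticians and quality control experts from other hospitals and universities". The relief judgement would already have been recorded at the bedside, and hiding the group later does not change it. The center also provides clinical decisions or recommendations, so some members may know the treatment.

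None of this answers the central point, that an impression without a stated threshold suffices for a primary category.

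**Conclusion.** The point holds in a limited form. The primary category *improved* can be reached on a symptom judgement alone, in a comparison where the treatment is evident and no masking is described. The likely direction is in favour of the granule. The size is unknown. Under the stated assumptions (pooled outcome, 135 per group, true rate 70%), upgrading 10% to 20% of the other granule patients gives a false-positive rate of 9% to 20% instead of about 5%, and less where many of them have worsened.

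The documents do not support the stronger conclusions that assessment was in fact open, that the CT scores are biased, or that a false-positive rate of 20% is to be expected. Groups are also not randomised, which the Discussion acknowledges, so 5% is itself an idealised reference.

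**What to change.** 1. Add a sensitivity analysis of the primary outcome in which patients who qualify as improved on the symptom item alone count as not improved. *Improved* then rests on two consecutive negative nucleic acid tests.
2. Report, by group, how many patients qualified by the symptom item only, the test item only, and both.
3. State with the result that recovery still requires respiratory symptoms to have disappeared, so the subjective element is reduced and not removed.
4. Where stored CT images are scored or rescored, hide group and visit day from whoever scores them. The article names no readers, so whether this needs extra staff cannot be judged from it.

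Section 4.1 says the trial is already in follow-up. Steps 1 to 3 use data already collected and need no new patient contact.

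The cost is one more table and a lower improved rate in that analysis. The CRF must also show which item qualified each patient, or hold the test results from which this can be derived. This should be checked first, because Table 1 has no separate row for nucleic acid testing.

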#### Second outcomes

2.10.2

1.Vital signs (d1-14), temperature, heart rate, blood pressure, respiratory rate (RR), oxygen saturation.2.Chest computed tomography (CT) score (d1, d7, d14), in our study we use high resolution computed tomography (HRCT). According to the existing scoring standards,^[22,23]^ each lobe will be graded. 0 points = no pathological changes of lung lobe, 1 point = pathological changes in 0% to 25% of lung lobes, 2 points = pathological changes in 25% to 50% of lung lobes, 3 points = pathological changes in 50% to 75% of lung lobes, 4 points = pathological changes in 75% to 100% of lung lobes, the total score of 5 lobes is used as the chest CT lesion score of each patient. We compare the mean value of lung CT scores.3.Inflammatory index (d1, d3, d5, d7, d14): peripheral hemogram (the count of peripheral blood leukocyte and lymphocyte), C-reactive protein (CRP), procalcitonin (PCT), tumor necrosis factor (TNF-a), interleukin-6 (IL-6), interleukin-10 (IL-10).4.Main organ function (d1, d3, d5, d7, d14): alanine aminotransferase (ALT), aspartate aminotransferase (AST), total serum bilirubin (STB), blood urea nitrogen (BUN), serum creatinine (Cr).5.Coagulation index (d0, d7, d14): blood platelet count (PLT), D-dimer, activated partial thromboplastin time (APTT), prothrombin time (PT), fibrinogen (Fg).6.Acute Physiology and Chronic Health Evaluation (d1, d3, d5, d7, d14, APACHE-II, Additional file 2) score: we compare the mean value of APECHA II the scores between 2 groups, and calculate improvement rate in APECHA II score = (d14 scored-0 score)/d0 score.

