### Data collection and management

2.14

We design the case report form (CRF) table as it presented in Additional file 5 by our study protocol. After collecting the information of patients, we will complete the CRFs rightly and timely. Then we input and organize them into an excel sheet. Finally, we will hand it over to statistical experts who will perform statistical analysis. The units of measurement should be unified. We will keep the personal and medical information of all patients strictly confidential. Statistical analysis results will be presented by publishing articles in professional journals or websites after finishing this study. The study procedure and assessments flowchart are as Table 1.

**Table 1 T1:** Study procedure and assessment.

		Observation node					Follow-up phase				
Study period	Visiting items	D1	D3	D5	D7	D14			1 year		
Screening stage	Inclusion criteria	X									
	Signing informed consent	X									
	Exclusion criteria	X									
	Matching and distribution	X									
Observation stage	Administration of study drug	X	X	X	X	X					
	Demographic	X									
	General Condition	X									
	Primary disease	X									
	Complication	X									
	Vital signs	X	X	X	X	X					
	Oxygenation index	X	X	X	X	X					
	Oxygen saturation	X	X	X	X	X					
	Chest CT	X		X		X					
	Hepatic function	X	X	X	X	X					
	Renal function	X	X	X	X	X					
	Cardiac function	X	X	X	X	X					
	Inflammatory indicators	X	X	X	X	X					
	Coagulation function	X	X	X	X	X					
	APACHEII score	X	X	X	X	X					
	Adverse event recording	X	X	X	X	X					
	Drug delivery/taking back/ destruction	X	X	X	X	X					
	Clinical outcomes					X					
	Safety evaluation	X	X	X	X	X					
Follow-up phase	LSAs								X		
	DASS21								X		

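### The APACHE II improvement rate has a sign opposite to its name and a d0 baseline scheduled nowhere; CT and coagulation days conflict with Table 1; scores are compared as raw means.

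*Protocol article*

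**What the plan says.** Section 2.10.2 lists the secondary outcomes with their days.

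- APACHE II: "Acute Physiology and Chronic Health Evaluation (d1, d3, d5, d7, d14, APACHE-II, Additional file 2) score". The same item compares mean scores between groups and adds an "improvement rate in APECHA II score = (d14 scored-0 score)/d0 score".
- CT: "Chest computed tomography (CT) score (d1, d7, d14", with the analysis given as "We compare the mean value of lung CT scores".
- Coagulation: "Coagulation index (d0, d7, d14".

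Table 1 in Section 2.14 has the observation columns "Visiting items D1 D3 D5 D7 D14" and no D0. It marks "APACHEII score X X X X X" and "Coagulation function X X X X X", that is, all five days for both. Its chest CT row is marked at D1, D5 and D14. The abstract also names only days 1, 3, 5, 7 and 14 for examinations.

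Section 2.12 compares continuous data with a t-test or a nonparametric test. Section 2.8 pairs the groups on gender, age and basic diseases. Section 3 acknowledges that the study is not randomised and includes only common-type patients.

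**The concern.** Three things need repair.

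First, the APACHE II formula. A fall in a severity score is an improvement, yet the formula makes it negative. It also refers to a baseline visit that is absent from the item's own list of days. A per-patient ratio has the further weakness that its denominator can be zero or very small.

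Second, the visit days. An analyst holding both Section 2.10.2 and Table 1 cannot tell which middle CT scan enters the analysis, or which coagulation values do. Those choices would be made after the data are in.

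Third, the comparison of raw means. Patients are grouped by whether they took the granule, and the pairing factors do not include the D1 CT or APACHE II score. A difference at D14 may then partly reflect a difference already present at D1.

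**Working it through.** **Days set side by side**

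| Outcome | Section 2.10.2 | Table 1 | Agree | Conflict |
|---|---|---|---|---|
| Chest CT | d1, d7, d14 | D1, D5, D14 | D1, D14 | d7 against D5 |
| Coagulation | d0, d7, d14 | D1, D3, D5, D7, D14 | D7, D14 | d0 has no column; D1, D3, D5 not in the text |
| APACHE II, days listed | d1, d3, d5, d7, d14 | D1, D3, D5, D7, D14 | all | none |
| APACHE II, baseline in the formula | d0 | no column | none | d0 scheduled nowhere |

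**Sign.** The printed formula has a typographical slip and is read here as (d14 − d0)/d0. The scores below are illustrative.

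- 10 to 5: (5 − 10)/10 = −50%, an improvement.
- 5 to 10: (10 − 5)/5 = +100%, a deterioration.
- 1 to 4: (4 − 1)/1 = +300%.
- 0 to 3: division by zero, undefined.

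Reversing the sign to (d0 − d14)/d0 gives +50% and −100% for the first two. That mends the name, but a baseline of 0 is still undefined.

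**Small denominators, if the ratio is computed per patient.** Take two patients, 20 to 10 and 2 to 6.

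- Ratios: (10 − 20)/20 = −0.50 and (6 − 2)/2 = +2.00.
- Mean of the ratios: (−0.50 + 2.00)/2 = +0.75.
- Ratio of the totals: (16 − 22)/22 = −27%.

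The mean ratio points to worsening while the total score falls, because the patient who started at 2 dominates.

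**Raw means against adjusted means.** Let r be the correlation between D1 and D14 scores within groups. The documents give no value; 0.5 to 0.7 is assumed.

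- Residual variance after adjustment for D1 is the fraction 1 − r²: 1 − 0.25 = 0.75 at r = 0.5, and 1 − 0.49 = 0.51 at r = 0.7, a reduction of 25% to 49%.
- Standard error factor: √0.75 = 0.866 and √0.51 = 0.714, a reduction of about 13% to 29%. This ignores the small loss from estimating the slope and from any D1 imbalance.
- With equal standard deviations at D1 and D14 and a linear relation, the slope is r. A D1 difference between groups then carries over by a factor of 0.5 to 0.7 into the raw D14 difference with no treatment effect at all.

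**The case against.** Several points can be made for the plan.

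- **d0 is probably just a label for D1.** Table 1 places screening, the baseline items and the first administration of study drug on D1. This is likely right. A reader might infer that no baseline was measured, or that all secondary outcomes hang on day 0. The documents do not support that: d0 appears in only two of the six items, and D1 values are scheduled for both. What stands is that the article never equates the two.
- **The sign is mainly a labelling matter.** The same formula applies to both groups, so a two-sided test gives the same p-value with either sign. This stands. The sign alone does not reverse the inferred treatment effect, but it can mislead whoever reads the reported rate.
- **The ratio may be meant for group means.** The article does not say, and the formula directly follows a comparison of means. On that reading the example gives −27%, in the right direction, and a zero denominator is practically impossible. The zero-baseline and +0.75 problems therefore depend on a per-patient reading. Low scores are plausible in common-type patients, but no distribution is given, so how often they occur is unknown.
- **Baseline is used for APACHE II.** The rate is relative to baseline, so it would be wrong to say that baseline is ignored for that score. It is ignored in the comparison of APACHE II means and in the CT analysis as stated.
- **Covariate adjustment may sit in an analysis plan not shown.** Its mere absence would be no finding. Here, however, the article states the comparison (means, by t-test or nonparametric test). Pairing on gender, age and basic diseases helps, but it does not cover D1 severity as scored.
- **Acute data collection should be over.** Recruitment was to end in June 2020, and Section 4.1 places the trial in follow-up. The remedy therefore lies in the analysis and reporting, not in instructing sites.

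**Conclusion.** The point holds for secondary outcomes only; the primary outcome and the planned 300 patients are untouched. The name and sign of the APACHE II rate disagree, given that a higher score is worse (the scale is in an additional file not shown), and its d0 is undefined. The CT middle day and the coagulation days contradict each other and must be reconciled; the documents do not show which is intended. The D1 and D14 CT scans and the D7 and D14 coagulation values are consistent in both places.

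Comparing raw means is a weak choice in this design, and a better one is available from measurements already scheduled. The gain of about 13% to 29% in standard error rests wholly on the assumed correlation of 0.5 to 0.7. A reader might infer that adjustment for D1 makes the groups comparable. It does not: it deals with the measured starting score and leaves other confounding in place. Nor can D1 be taken as pre-treatment, because Table 1 also marks drug administration on D1 and gives no order of events.

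**What to change.** 1. State that d0 means the D1 assessment, and confirm from the case report forms that it preceded the first dose. Report any patient for whom it did not.
2. Replace the APACHE II ratio with the between-group difference in D14 score adjusted for the D1 score, by ANCOVA or a mixed model over the scheduled visits. Do the same for the CT score.
3. Reconcile the CT and coagulation days between Section 2.10.2 and Table 1. Analyse CT by the day actually recorded, and report how many middle scans fell on each day.
4. Describe the adjusted results as associations in a non-randomised cohort.

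The cost is wording and programming on data already scheduled, plus a check of the recorded times and days. If the middle scan was taken on different days at different centres, wording alone will not restore a common time point, and that comparison will be weaker. The D14 comparison is not affected.
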